#### Use of Drivingly Online materials

Data on parent and teen online engagement will be captured using passive web-tracking enabled on the Drivingly web platform and tagged to log-in credentials. Thus, we will be able to evaluate engagement with the various components of the psychoeducational curriculum. This information will be used for quality improvement and for any “as-treated” analyses.

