**Methods:**

Eligible participants are aged 16-17.33 years of age, have a learner’s permit in Pennsylvania, have practiced no more than 10 h, and have at least one parent/caregiver supervising. Participants are recruited from the general community and through the Children’s Hospital of Philadelphia’s Recruitment Enhancement Core. Teen-parent dyads are randomized 1:1 to Drivingly or usual practice control group. Drivingly participants receive access to an online curriculum which has 16 lessons for parents and 13 for teens and an online logbook; website usage is tracked. Parents receive two, brief, psychoeducational sessions with a trained health coach and teens receive an on-road driving intervention and feedback session after 4.5 months in the study and access to DriverZed, the AAA Foundation’s online hazard training program. Teens complete surveys at baseline, 3 months post-baseline, at licensure, 3months post-licensure, 6 months post-licensure, and 12 months post-licensure. Parents complete surveys at baseline, 3 months post-baseline, and at teen licensure. The primary end-point is police-reported MVCs within the first 12 months of licensure; crash data are provided by the Pennsylvania Department of Transportation.

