*Parent-Sessions and Psychoeducational learning-to-drive Curriculum*: Parents receive two, brief, psychoeducational sessions with a trained health coach. The first parent session is an orientation to the program and the learner period, and the second parent session occurs while the teen is taking their ODA and is focused on readiness to drive and keeping teens safe after licensure. These sessions are delivered via a systematic health coach training process and training manual which includes a script to ensure consistency in the delivery of key messages. In complement to these sessions, parents and teens are supported with a web-based psychoeducational curriculum tailored to each stage of GDL and provided with sample conversation starters and activities to clarify goals and expectation for safe driving. The web-based psychoeducational curriculum contains 16 lessons for parents and 13 for teens, plus an online logbook. Structured using the Health Belief Model, 36] the curriculum entails an overview of risk factors for adolescents’ MVCs, the importance of the parental role as practice supervisor and risk-reducer, strategies for overcoming barriers to engagement, and reviews Pennsylvania’s GDL programme. The curriculum consists of two parts. Part 1 is aligned with the permit period and focuses on how to achieve high quality practice driving. There is also a complete practice driving curriculum based on the Drivingly **C**ommunicate **A**nticipate **R**egulate (CAR) Zone system. CAR scaffolds parents’ supervision by clearly defining driving zone specific targets for teens to practice in the domains of communication, anticipation and regulation (e.g., Communicate – Commercial Zone: Look and listen for other drivers and pedestrians trying to communicate with you). Part 2 is aligned with the restricted (or intermediate) license period and scaffolds parents’ involvement during the first year of licensure focusing on parental enforcement of GDL and planning for difficult social situations (e.g., impaired driving).

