### Statistical plan

With an initial sample size of 600 Drivingly dyads and 600 controls assuming 10% dropout in each group, a 1-year post-licensure crash risk in the unexposed group of 15%, and significance level (α) of 0.05, we will have 90% power to detect a hazard ratio (HR) of 0.59 for the first year of licensure. Alternatively, assuming a first-year control group crash rate of 20% the detectable HR is 0.65 for the first year of licensure; assuming a 25% first-year crash rate, the detectable HR is 0.69 [38]. Given our prior observed reduction of the ODA on crash risk of 53% (adjusted HR 0.47), these detectable HRs are conservative. Specifically, if the true HR is 0.47, we will have 99.4% power if the control group crash rate is 15%.

Risk ratios comparing the risk of any MVC involvement between Drivingly and Control will be estimated using modified Poisson regression [39]. Time-to-event (survival) analysis will be conducted to examine time to first MVC (from time of enrolment and from intermediate licensure) as the primary dependent variables of interest. We will create Kaplan-Meier curves to graphically depict the probability of these outcomes and compare the distributions of the two groups (Drivingly vs. Control) using the log-rank test. We will use a Cox proportional hazards (PH) model to estimate unadjusted hazard ratios, using an exact method for handling tied event times. To determine if there is effect modification by gender, we will use a PH model with a multiplicative interaction between gender and group (Drivingly vs. Control) and assess significance at the 0.10 level. We will report gender-specific hazard ratios between the Drivingly and Control groups because male drivers are at greater risk for MVCs than female drivers [40, 41].

To evaluate Drivingly’s conceptual model (Fig. 1) we will use marginal structural models with VanderWeele’s decomposition formulas for mediation analyses [42] This counterfactual approach to mediation analysis allows for the decomposition of total effects into direct and indirect components so we can estimate the proportion of the total effect of Drivingly on MVC risk mediated by each hypothesized process variable [42].

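### The only inferential use named for web-engagement data is as-treated analysis, which can show a benefit when there is none; a one-sentence rewording would protect any adherence analysis.

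*Protocol article*

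**What the plan says.** Under Use of Drivingly Online materials, the protocol article says that engagement is "captured using passive web-tracking enabled on the Drivingly web platform and tagged to log-in credentials". It then gives the purpose: "This information will be used for quality improvement and for any “as-treated” analyses". No outcome, engagement threshold, comparator or status is attached to those analyses.

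The Methods part of the abstract places the curriculum in the intervention arm: Drivingly families get "an online curriculum which has 16 lessons for parents and 13 for teens and an online logbook; website usage is tracked". Description of Drivingly adds that "Part 2 is aligned with the restricted (or intermediate) license period and scaffolds parents’ involvement during the first year of licensure".

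The Statistical plan section compares the randomised groups. For the risk ratio: "Risk ratios comparing the risk of any MVC involvement between Drivingly and Control will be estimated using modified Poisson regression". For time to first crash, the plan will "compare the distributions of the two groups (Drivingly vs. Control) using the log-rank test". Neither uses engagement, and the section mentions no as-treated or other adherence-based analysis.

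**The concern.** In its ordinary sense, an as-treated analysis groups participants by what they received, not by the arm to which they were allocated. Here, what was received is what the family chose to do on a website after randomisation. There are two routes to bias.

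- **Selection.** The article's Background cites evidence that involved parent supervisors benefit teen drivers. Parents who work through the lessons are plausibly those parents, so their teens may crash less often whatever the lessons do.
- **Timing.** Part 2 of the curriculum is used in the same year in which crashes are counted. A teen who stays crash-free has longer to accumulate engagement, and a crash may itself change how the family uses the site.

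At stake is a supplementary result, not the primary one. If such a result were reported, it could look more favourable than the randomised comparison. It would also reintroduce the weakness, lack of random assignment, that the article's Discussion abstract criticises in earlier evaluations.

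**Working it through.** The plan gives no figure for engagement or for its relation to crash risk, so there is nothing of its own to reproduce on this point. The check asks what an as-treated contrast would show if Drivingly did nothing.

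**Inputs from the Statistical plan section**
- 600 dyads per arm less 10% dropout: 600 × 0.90 = 540 per arm.
- One-year control crash risk 15%; under the null, 15% in both arms.
- Significance level 0.05, taken here as two-sided because the article does not say.

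**Assumptions**
- Share of the Drivingly arm engaged: e = 0.60.
- Intrinsic crash risk of engaged relative to non-engaged families: r = 0.9, 0.8, 0.7 or 0.6.
- Comparator: engaged families against all other dyads, one reading of as-treated.

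**Formulas**
- Non-engaged risk: pn = 0.15 / (e·r + 1 − e).
- Engaged risk: pe = r·pn.
- Engaged number: 540 × 0.60 = 324. All others: 216 non-engaged + 540 controls = 756.
- Risk in all others: po = (216·pn + 540 × 0.15) / 756.
- Apparent risk ratio: pe / po.
- The last column below is the normal-approximation chance that a two-proportion test of 324 against 756 is significant in favour of engagement.

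**Example, r = 0.7.** pn = 0.15 / (0.42 + 0.40) = 0.1829; pe = 0.1280; po = (39.5 + 81) / 756 = 0.1594; ratio = 0.1280 / 0.1594 = 0.80.

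| r | pn | pe | po | Apparent risk ratio | Chance of a false significant benefit |
|---|---|---|---|---|---|
| 0.9 | 0.1596 | 0.1436 | 0.1527 | 0.94 | 6% |
| 0.8 | 0.1705 | 0.1364 | 0.1558 | 0.875 | 12% |
| 0.7 | 0.1829 | 0.1280 | 0.1594 | 0.80 | 25% |
| 0.6 | 0.1974 | 0.1184 | 0.1635 | 0.72 | 48% |

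The comparison of the arms as randomised gives a ratio of 1.00 and a 2.5% chance of a false significant benefit. Comparing engaged families with controls only does not remove the selection: at r = 0.7 the ratio is 0.1280 / 0.15 = 0.85.

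**Range.** With e from 0.30 to 0.70 and r from 0.9 to 0.5, the apparent ratio runs from 0.95 to 0.55, and the chance of a false significant benefit from about 5% to 78%.

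**Does a complier-average estimate do better?** It depends on how receipt is defined. The complier-average ratio divides the treated compliers' risk by the risk implied for compliers among controls: (0.15 − 0.40 × observed non-complier risk in the Drivingly arm) / 0.60. Take r = 0.7.
- *Effect of 0.70 in engaged families only.* Treated engaged risk = 0.70 × 0.1280 = 0.0896. Implied control complier risk = (0.15 − 0.40 × 0.1829) / 0.60 = 0.1280. Complier-average ratio = 0.70, the truth. As-treated = 0.0896 / 0.1594 = 0.56.
- *Effect of 0.70 across the whole arm (through coaching and the on-road assessment), with receipt defined by web engagement alone.* Non-engaged risk becomes 0.70 × 0.1829 = 0.1280. Implied control complier risk = (0.15 − 0.40 × 0.1280) / 0.60 = 0.1646. Complier-average ratio = 0.0896 / 0.1646 = 0.54. As-treated = 0.0896 / [(216 × 0.1280 + 81) / 756] = 0.0896 / 0.1437 = 0.62.

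In the second case both estimates overstate the effect, and the complier-average one is further from 0.70. Receipt must therefore cover every component, not only lessons.

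**The case against.** The strongest reply is that no as-treated analysis is actually planned. The sentence stands in a measurement subsection, says only *any* such analyses, and puts the term in quotation marks. The definition of an optional adherence analysis is commonly left to the SAP or full protocol, which are not shown. That stands, and it limits the point to the choice of method named. The missing detail is not criticised here.

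A reader might infer that the trial's efficacy conclusion will rest on engaged families compared with everyone else. The article does not support that. It specifies no such comparator, it presents no as-treated result as evidence of efficacy, and its stated group comparisons use the randomised arms.

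It is also fair to say that the size follows from assumed inputs. With weak selection (10%) the false-benefit rate is about 6%, little above the 2.5% of the randomised comparison. Adjustment for the baseline variables collected might remove part of the selection; the calculation includes none.

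Two objections to the remedy also hold in part. A complier-average estimate based on web use alone can mislead, as shown above, so the definition of receipt matters. One-sided non-adherence is also not fully established: the Surveys section has dyads logging practice on the Drivingly platform without naming an arm.

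What remains is that the article names one inferential method for these data, and that method gives up the protection of randomisation.

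**Conclusion.** The point holds as a minor improvement. The primary result is unaffected. Any as-treated contrast that is run would be open to selection, and to bias from engagement that accrues while crashes are counted.

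Under a true null with 60% engaged and 10% to 40% lower intrinsic risk in engaged families, the apparent risk ratio is about 0.94 to 0.72. Only the 540 per arm and the 15% come from the plan. The engaged share, the strength of selection and the comparator are assumptions, and the timing bias is not quantified. The calculation shows what could happen; it is not a forecast for this trial.

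**What to change.** In Use of Drivingly Online materials, replace the as-treated wording with text to this effect: efficacy conclusions rest on all dyads as randomised; engagement data serve quality improvement; any adherence analysis is a secondary or exploratory complier-average analysis with randomised arm as instrument, keeping all randomised dyads.

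Define receipt before crash records are linked, as having started any Drivingly component. A web-lesson cut-off alone should not be used, because coaching and the on-road assessment could affect families below the cut-off and so violate the exclusion restriction.

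Confirm that control dyads cannot open the curriculum, including through any practice log they use on the Drivingly platform.

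The cost is a change of wording and, if it is run, one further analysis on data already collected. The interval will be wider than for an as-treated contrast, and the method assumes no effect in families who started nothing. If nearly every family starts something, the estimate will lie close to the randomised comparison and add little to it.

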#### Surveys

Survey collection from teens will occur at baseline, 3 months post-baseline, licensure, 3 months post-licensure, 6 months post-licensure, and 12months post-licensure. Survey collection from parents will occur at baseline, 3 months post baseline, and at teen licensure. Survey collection will be done remotely, through REDCap. Missed survey responses may be followed up by phone, text, or email with the study team. Additionally, dyads will be asked to record/log their practice driving for 5–6 months post-baseline and prior to obtaining their driver’s license via a web-based e-learning platform (via the Drivingly WordPress platform). See Supplementary Table 1 for a summary of survey measures mapped to the Drivingly Conceptual Model. In addition, we measured driving exposure two ways at baseline, 3, 6, 9, 12 and 18 months with The Situational Driving Frequency Scale [37] to assess driving frequency in 14 situations using 5-point scale ranging from Never (0) to Very Often (4 to 7 days per week); total score 0–56 (teen report; parent report at Baseline only) and hours of driving per week was assessed using a write-in of hours driven Monday-Friday; Saturday and Sunday at (teen and parent report). Sociodemographic data were collected at baseline and included teen and parent gender, age, race and ethnicity, and parent’s relationship to teen, educational attainment, and current relationship status. Additional individual difference variables were collected but are not the focus of the main trial (e.g., sensation seeking) and are thus not reported here.

### Statistical plan

With an initial sample size of 600 Drivingly dyads and 600 controls assuming 10% dropout in each group, a 1-year post-licensure crash risk in the unexposed group of 15%, and significance level (α) of 0.05, we will have 90% power to detect a hazard ratio (HR) of 0.59 for the first year of licensure. Alternatively, assuming a first-year control group crash rate of 20% the detectable HR is 0.65 for the first year of licensure; assuming a 25% first-year crash rate, the detectable HR is 0.69 [38]. Given our prior observed reduction of the ODA on crash risk of 53% (adjusted HR 0.47), these detectable HRs are conservative. Specifically, if the true HR is 0.47, we will have 99.4% power if the control group crash rate is 15%.

Risk ratios comparing the risk of any MVC involvement between Drivingly and Control will be estimated using modified Poisson regression [39]. Time-to-event (survival) analysis will be conducted to examine time to first MVC (from time of enrolment and from intermediate licensure) as the primary dependent variables of interest. We will create Kaplan-Meier curves to graphically depict the probability of these outcomes and compare the distributions of the two groups (Drivingly vs. Control) using the log-rank test. We will use a Cox proportional hazards (PH) model to estimate unadjusted hazard ratios, using an exact method for handling tied event times. To determine if there is effect modification by gender, we will use a PH model with a multiplicative interaction between gender and group (Drivingly vs. Control) and assess significance at the 0.10 level. We will report gender-specific hazard ratios between the Drivingly and Control groups because male drivers are at greater risk for MVCs than female drivers [40, 41].

To evaluate Drivingly’s conceptual model (Fig. 1) we will use marginal structural models with VanderWeele’s decomposition formulas for mediation analyses [42] This counterfactual approach to mediation analysis allows for the decomposition of total effects into direct and indirect components so we can estimate the proportion of the total effect of Drivingly on MVC risk mediated by each hypothesized process variable [42].

If there is substantial item-level missingness in the survey data (e.g., in excess of 5%), we will assess whether non-response bias may be present; however, if we find such differences, we will use multiple imputation with chained equations as suggested by prior research under the relatively mild assumption of missingness at random [43].

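### The power paragraph does not say whether alpha is one- or two-sided; read as two-sided 0.05, power at the printed hazard ratios is about 81–85%, not 90%

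*Protocol article*

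**What the plan says.** The Statistical plan of the protocol article opens with the sample size: "With an initial sample size of 600 Drivingly dyads and 600 controls assuming 10% dropout in each group". Its other inputs are a base-case control risk of 15% over the first licensed year and an alpha of 0.05 with no mention of sides. Randomisation is 1:1 (Abstract, Methods). From these inputs it derives four figures:

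- base case: "we will have 90% power to detect a hazard ratio (HR) of 0.59 for the first year of licensure";
- at 20% control risk: "assuming a first-year control group crash rate of 20% the detectable HR is 0.65 for the first year of licensure";
- at 25% control risk: a hazard ratio of 0.69, on the same terms;
- at a true hazard ratio of 0.47: "we will have 99.4% power if the control group crash rate is 15"%.

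The 0.47 is the adjusted hazard ratio seen earlier for the on-road driver assessment, and the plan calls its detectable hazard ratios conservative beside it. The same section names time to first crash as the primary dependent variable, compared by the log-rank test and a Cox model. No power formula is given, only a literature citation.

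**The concern.** The section gives every input to a standard event-based power calculation except the sidedness of the test. With the usual two-sided reading, the expected number of first crashes falls short of what 90% power requires in all three scenarios. The type II error at the printed effects would then be roughly 15–19% instead of 10%. Anyone interpreting a null result would be judging it against a detectable effect that the design does not have at the stated power.

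**Working it through.** **Inputs.** 600 per arm, 10% dropout, control risks of 15%, 20% and 25%, alpha 0.05, hazard ratios 0.59, 0.65, 0.69 and 0.47 (all from the Statistical plan); 1:1 allocation and 12 months from licensure (Abstract). Two assumptions are added: dropouts contribute nothing, so 600 × 0.9 = 540 per arm, and hazards are proportional.

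**Formulas.** Intervention risk p1 = 1 − (1 − p0)^HR. Expected events d = 540 × (p0 + p1). Schoenfeld power = Φ(|ln HR| × √d / 2 − z), with z = 1.960 (two-sided) or 1.645 (one-sided). Events needed for 90% power = 4 × (z + 1.2816)² / (ln HR)².

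**Base case, two-sided.** p1 = 1 − 0.85^0.59 = 0.0914; d = 540 × 0.2414 = 130.4; |ln 0.59| = 0.5276; 0.5276 × √130.4 / 2 = 3.012; Φ(3.012 − 1.960) = 85.4%. Events needed: 4 × (3.2416)² / 0.5276² = 151.0.

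**All scenarios, Schoenfeld, 540 per arm**

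| Control risk | HR | Printed power | Expected events | Events needed for 90%, two-sided | Power, two-sided | Power, one-sided |
|---|---|---|---|---|---|---|
| 15% | 0.59 | 90% | 130 | 151 | 85.4% | 91.4% |
| 20% | 0.65 | 90% | 181 | 226 | 82.6% | 89.5% |
| 25% | 0.69 | 90% | 232 | 305 | 80.7% | 88.1% |
| 15% | 0.47 | 99.4% | 121 | – | 98.6% | 99.4% |

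**Hazard ratio detectable with 90% power, 540 per arm**

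| Control risk | Printed | Two-sided 0.05 | One-sided 0.05 |
|---|---|---|---|
| 15% | 0.59 | 0.564 | 0.600 |
| 20% | 0.65 | 0.614 | 0.647 |
| 25% | 0.69 | 0.650 | 0.680 |

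**Sensitivity of the two-sided result at the three printed hazard ratios**

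- Freedman's formula: 83.8%, 81.4%, 79.8%.
- Simulated log-rank test, 4,000 trials per scenario: 84.4%, 82.2%, 80.1%.
- No dropout at all, 600 per arm: 88.8%, 86.3%, 84.6%.

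No two-sided log-rank variant that was tried reaches 90% in all three scenarios, even with dropout ignored.

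**Can the printed figures be reproduced?** Two calculations come close; neither gives all four.

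- One-sided 0.05 Schoenfeld with 540 per arm gives 99.4% at 0.47 exactly. Its detectable hazard ratios round to 0.60, 0.65 and 0.68, against the printed 0.59, 0.65 and 0.69. The two misses run in opposite directions.
- A two-sided test on the log risk ratio, with the printed values read as risk ratios and the full 600 per arm, gives detectable ratios of 0.589, 0.649 and 0.691, which match to two decimals. At 0.47 it gives 98.9%, not 99.4%.

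**The case against.** The strongest reply is that two-sidedness is not in the document. The hypothesis is directional, and a one-sided 0.05 test with the stated dropout gives power within 2 points of each printed 90% and matches the 99.4% to the decimal. This stands: a reader might conclude outright that the trial does not deliver 90% power, and the text does not support that without the two-sided condition. It does not clear the paragraph, though. A directional hypothesis is not a declared one-sided test, an unqualified alpha of 0.05 is ordinarily taken as two-sided, and the one-sided calculation still misses at 15% and 25% risk.

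Second, treating every dropout as lost is an assumption. Crash records come from the state transportation department for all licensed participants, so a teen who stops answering surveys need not lose the outcome. That is fair, but counting all 600 per arm still gives only 85–89% two-sided. One-sided, with dropouts contributing half (570 per arm), the detectable hazard ratios are 0.609, 0.655 and 0.688; this recovers 0.69 and moves further from 0.59.

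Third, a reader might infer that the printed values are risk ratios mislabelled as hazard ratios with dropout left out. The match to the three ratios is suggestive, but the same calculation fails on the fourth figure and the cited method is not available here. The source of the figures cannot be determined from the document.

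Fourth, a reader might infer that the claim of conservatism falls. It does not: the two-sided detectable hazard ratio of 0.56 at 15% risk is still well above 0.47, and power at 0.47 is about 98.6%. Nor does the document give a figure for teens who never become licensed that would justify a further reduction in power.

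**Conclusion.** The point holds conditionally. If the primary log-rank or Cox test is two-sided at 0.05, the paragraph overstates power at its printed hazard ratios by about 5, 7 and 9 percentage points at control risks of 15%, 20% and 25%, and the 99.4% by about 0.8 points. If the test is one-sided at 0.05, the figures are nearly right, but the sidedness is undeclared and the hazard ratios at 15% and 25% risk are each off by 0.01. Either way the paragraph needs correcting. The sizes rest on proportional hazards, a full licensed year for each retained teen, and 540 evaluable per arm. Under Schoenfeld's formula two-sided power stays above 80% throughout; Freedman's puts the 25% scenario just under it. The adequacy of the sample size for an effect near 0.47 is not in doubt.

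**What to change.** State the sidedness of the primary test and the power formula, then correct the figures to match:

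- **If two-sided 0.05:** give the hazard ratios detectable with 90% power as about 0.56, 0.61 and 0.65 at control risks of 15%, 20% and 25%, or keep the printed hazard ratios and give power as about 85%, 83% and 81%. Change 99.4% to about 98.6%. Add the expected numbers of first crashes, about 130, 181 and 232 at the printed hazard ratios.
- **If one-sided 0.05 was intended:** say so, and give the detectable hazard ratios as about 0.60, 0.65 and 0.68. The 99.4% can stay.

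In both cases, say how dropout enters the calculation. The cost is a few sentences of wording and, if two-sided, slightly less favourable detectable effects. Sample size, endpoint and analysis are unchanged.

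### The Cox hazard ratio is planned as unadjusted; pre-specifying an overall covariate-adjusted estimate would be a small, nearly free improvement

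*Protocol article*

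**What the plan says.** All of the analysis text is in the Statistical plan section of the protocol article.

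- Outcome: survival analysis will "examine time to first MVC (from time of enrolment and from intermediate licensure) as the primary dependent variables of interest".
- Test: Kaplan-Meier curves are drawn, and the plan will "compare the distributions of the two groups (Drivingly vs. Control) using the log-rank test".
- Estimate: "We will use a Cox proportional hazards (PH) model to estimate unadjusted hazard ratios", with ties treated exactly.
- Gender: for effect modification, "we will use a PH model with a multiplicative interaction between gender and group (Drivingly vs. Control) and assess significance at the 0.10 level". Gender-specific hazard ratios will be reported "because male drivers are at greater risk for MVCs than female drivers".
- Other analyses: risk ratios from modified Poisson regression are also planned and are not labelled adjusted or unadjusted.

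The Surveys section lists what is available before any treatment effect can act: "Sociodemographic data were collected at baseline and included teen and parent gender, age, race and ethnicity". It also lists baseline driving exposure, measured by a situational frequency scale and by weekly hours. The Recruitment procedures section says only that a table of random numbers is used for randomisation; it mentions no stratification.

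**The concern.** The plan identifies a prognostic factor, records it at baseline, and then specifies a headline hazard ratio that ignores it. The interaction model does not fill the gap. It yields one hazard ratio for males and one for females, and no single overall effect with gender held constant.

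Two things are given up. One is a little precision, because in a randomised trial conditioning on prognostic baseline variables usually raises power slightly. The other is protection of the overall estimate against a chance difference between arms in gender mix. There is also a procedural stake: if no covariate list is fixed in advance and an imbalance appears, any adjustment added later is open to the charge that it was chosen after seeing the data.

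**Working it through.** **1. The plan's own power figure, which involves no covariates.** Inputs from the Statistical plan: 600 per arm, 10% dropout, 15% control risk, hazard ratio (HR) 0.59, α 0.05 with sidedness not stated.

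- Evaluable per arm: 600 × 0.90 = 540.
- Intervention risk under proportional hazards: 1 − 0.85^0.59 = 0.0914.
- Expected events: 540 × (0.15 + 0.0914) ≈ 130.
- Schoenfeld: √130.4 / 2 × |ln 0.59| = 5.709 × 0.5276 = 3.012.
- One-sided: Φ(3.012 − 1.645) = 91.4%. Two-sided: Φ(3.012 − 1.960) = 85.4%. The plan states 90%.

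The one-sided calculation comes within 2 points of the plan's other figures too: 89.5% at HR 0.65, 88.2% at HR 0.69 and 99.4% at HR 0.47. This step only fixes the starting point for what follows.

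**2. Size of a chance gender imbalance.** Assumptions: simple randomisation, 50:50 gender split, male HR 1.5.

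- SD of the between-arm difference in male share: √(2 × 0.25 / 540) = 0.030, so the 95% range is about ±6 percentage points.
- Shift in the estimated HR at the edge of that range: (1 + 0.5 × 0.53) / (1 + 0.5 × 0.47) = 1.265 / 1.235 = 1.024, or about 2.4%.
- Sampling error for comparison: SE(log HR) ≈ 2/√130 = 0.175, so the 95% limits are the estimate multiplied by about 0.71 and 1.41. The shift on the log scale, ln 1.024 = 0.024, is about 0.024 / 0.175 = 0.14 of one standard error.

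**3. Power with and without adjustment.** Simulated Cox models: 540 per arm, one-year censoring, 15% control risk, true HR 0.59, two-sided 0.05. Covariate effects are assumed.

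| Baseline covariate (assumed HR) | Unadjusted | Adjusted | Runs |
|---|---|---|---|
| Gender, 1.25 | 83.9% | 83.9% | 6,000 |
| Gender, 1.5 | 83.7% | 83.9% | 6,000 |
| Gender, 2.0 | 83.8% | 84.4% | 6,000 |
| Gender, 3.0 | 84.1% | 84.3% | 1,500 |
| Continuous, 1.5 per SD | 83.3% | 84.4% | 6,000 |
| Continuous, 2.0 per SD | 83.2% | 85.7% | 1,500 |

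A separate simulation (5,000 runs each) compared unstratified with stratified analysis on a 50:50 covariate:

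- HR 1.3: 84.5% against 84.7%
- HR 1.5: 84.0% against 84.3%
- HR 2.0: 83.4% against 83.6%
- HR 3.0: 83.2% against 83.9%

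Across both sets, gender alone adds about 0 to 0.7 points, and a continuous predictor of the assumed strength about 1 to 2.5 points. The Monte Carlo standard error of one power figure at 6,000 runs is √(0.84 × 0.16 / 6,000) ≈ 0.5 points, and about 0.9 points at 1,500 runs. The gender gains should therefore be read as small and not as exact.

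**4. Validity and the quantity estimated.** Under the null with gender HR 2.0, type I error was 5.2% unadjusted and 4.7% adjusted. With true HR 0.59 and gender HR 2.0, the mean estimated HR was 0.588 unadjusted and 0.586 adjusted.

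**The case against.** The strongest reply is that nothing in the plan is wrong. A log-rank test and an unadjusted Cox model are valid after 1:1 randomisation, and the standard error already allows for chance imbalance. The gain from gender is under one point of power. Gender is not ignored either: the gender-specific hazard ratios compare the arms within gender and so are unaffected by gender imbalance. An adjusted analysis or stratified randomisation may also be described in a full protocol or SAP that is not shown. All of this stands, and it limits the point to an improvement. It does not remove the point, because the article expressly fixes the estimate as unadjusted and neither the interaction model nor the gender-specific results give an adjusted overall effect.

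A reader might infer more than the document supports:

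- **That strong predictors are being discarded.** The article gives a direction for gender and no effect size for any covariate. Eligibility limits age to 16 to 17.33 years and prior practice to 10 hours, so age and baseline exposure may have little range.
- **That adjustment would make the result comparable with the earlier on-road assessment (ODA) estimate**, cited as "our prior observed reduction of the ODA on crash risk of 53% (adjusted HR 0.47". At about 15% risk the two kinds of hazard ratio barely differ (0.588 against 0.586). The earlier covariates are not given, and the assessment was then an outcome measure and is now one component of the programme.
- **That power is already below the stated 90%.** That depends on the unstated sidedness of α. It is a separate question, and adjusting for gender would not settle it.

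**Conclusion.** The point holds as a low-severity improvement. The planned unadjusted analysis is sound, and a reader should not conclude that it is biased or that its error rate is inflated. What the plan lacks is a pre-specified overall effect adjusted for baseline variables it already collects, one of which it calls prognostic itself. The benefit is about 0 to 0.7 points of power from gender alone, and about 1 to 2.5 points if some baseline predictor has a hazard ratio of 1.5 to 2.0 per SD. It also protects the overall estimate against an imbalance that could move the hazard ratio by about 2.4% at the edge of its 95% range. These sizes rest on an assumed 50:50 gender split, assumed covariate effects, 540 evaluable teens per arm and a 15% control risk. The direction of the advice does not depend on those assumptions, because the cost is close to nil.

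**What to change.** Before outcome data are analysed, amend the Statistical plan as follows:

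- Make the primary Cox hazard ratio one adjusted for teen gender, age at enrolment and baseline driving exposure. Name which of the two exposure measures is used, its functional form, and how missing baseline values are handled so that no randomised dyad is dropped.
- Stratify the log-rank test by gender.
- Report the unadjusted hazard ratio beside the adjusted one, and keep the planned interaction model and gender-specific results.
- Exclude every variable measured after randomisation, such as age at licensure or driving exposure recorded after baseline.

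If a full SAP already contains such an analysis, aligning the two texts is enough. No new data are needed; the cost is a few sentences and a few lines of analysis code.
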